### **4.3. Malaria epidemiology and control in the study area**

Malaria transmission in the study area is intense and there is little seasonal variability in transmission rates or parasite prevalence [Wildling 1995; Sylla 2001]. *Plasmodium falciparum* is the predominant species and responsible for 95% of all infections. The main vectors are *Anopheles gambiae* and *An. moucheti*. The entomological inoculation rate lies around 50 infective bites per person per year [Sylla 2000].

The level of chloroquine resistance is high, reaching 100% both in vitro and in vivo [Borrmann 2002]. Resistance of local parasite strains to sulfadoxine/pyrimethamine is moderate and rising steadily. A recent study in Lambaréné found a treatment failure of 21% in children on Day 14 [Allouche 2004]. The policy of the government of Gabon is to treat all children with malaria with Artemisinin-based Combination Therapy (ACT).

On average, children aged 2 to 12 years experience about 1.5 malarial attacks per year, with large variability among individuals [[name] 1999]. Anemia is common: around 70% of children tested at HAS MRU have Hb < 9g/dL; about 17% of children have Hb < 5g/dL [[name] unpublished].

There is no widely implemented national or local bednet programme. Although part of the population sleep under bednets, these are rarely impregnated, installed properly or well-maintained.

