#### **4.7. Exclusion criteria for enrolment**

The following criteria should be checked at the time of study entry. If any apply, the subject must not be included in the study:

- Acute disease at the time of enrolment (acute disease is defined as the presence of a moderate or severe illness with or without fever). All vaccines can be administered to persons with a minor illness, such as diarrhea or mild upper respiratory infection without fever, i.e. axillary temperature < 37.5°C.

- Serious acute or chronic illness determined by clinical or physical examination and laboratory screening tests including, but not limited to:
  - Any confirmed or suspected immunosuppressive or immunodeficient condition, based on medical history and physical examination (no laboratory testing required)
  - A family history of congenital or hereditary immunodeficiency
  - History of splenectomy
  - Major congenital defects
  - History of any neurologic disorders or seizures
  - Moderate malnutrition at screening defined as weight for age Z-score less than -2.
- Laboratory screening tests out of range, specifically:
  - refer to Table 10
- Planned administration/administration of a vaccine not foreseen by the study protocol within 30 days of the first dose of vaccine(s) with the exception of tetanus toxoid.
- Use of any investigational or non-registered drug or vaccine within 30 days preceding the first dose of study vaccine, or planned use during the study period.
- Administration of immunoglobulins, blood transfusions or other blood products within the three months preceding the first dose of study vaccine or planned administration during the study period.
- Chronic administration (defined as more than 14 days) of immunosuppressants or other immune-modifying drugs within six months prior to the first vaccine dose (for corticosteroids, this will mean prednisone, or equivalent,  $\geq 0.5$  mg/kg/day. Inhaled and topical steroids are allowed).
- Previous participation in any other malaria vaccine trial.
- Simultaneous participation in any other clinical trial.
- Same sex twin.
- History of allergic reactions (significant IgE-mediated events) or anaphylaxis to previous immunizations.
- History of allergic disease or reactions likely to be exacerbated by any component of the vaccine.
- Any other findings that the investigator feels would increase the risk of having an adverse outcome from participation in the trial.

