## **5.6. Monitoring of hematological and biochemical laboratory parameters**

Blood for safety monitoring of hematology, renal and hepatic function will be measured at screening, one week post Dose 1, one month post Dose 3 and 12 months post Dose 3. The hematological and biochemical parameters will be documented on the CRF. For all values outside the normal range (refer to Table 10), the reason and/or clinical condition will be documented. Results of hematological and biochemical laboratory tests will be reviewed as soon as they are generated. Any value outside the normal range will be managed as appropriate by a medically qualified individual under the supervision of the Principal Investigator (refer to Section 8.6). Guidance on when to report abnormalities as SAEs is given in Section 8.3.

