### **6.5. Method of blinding and breaking the study blind**

Data pertaining to RTS,S/AS02D or RTS,S/AS01E will be collected in a double blinded (observer blinded) manner. 'Double blinded (observer blinded)' means that the vaccine recipient and their parent(s)/guardian(s) as well as those responsible for the evaluation of safety and immunogenicity endpoints will all be unaware which treatment, RTS,S/AS02D or RTS,S/AS01E, was administered to a particular subject. The only study staff aware of the vaccine assignment for RTS,S/AS02D or RTS,S/AS01E will be those responsible for the storage and preparation of vaccines; these staff will play no other role in the study.

Code break envelopes, for each study enrolled subject and associating each treatment number with a specific vaccine, will be kept by the Local Safety Monitor in Gabon as well as by Central Safety at GSK Biologicals, Rixensart in a safe and locked place with no access for unauthorized personnel.

If deemed necessary for reasons such as safety, the Local Safety Monitor in Gabon as well as GSK Biologicals Central Safety will unblind the specific enrolled subject without revealing the study blind to the investigators.

As part of the safety monitoring plan, safety reports will be produced at two timepoints in the trial (refer to 5.1.3.3). An independent statistician will analyze the data, thereby maintaining the blind of the malaria project team at GSK Biologicals and the investigator group.

A formal reporting and analysis plan (RAP) will be developed. Once the study is completed and the GSK Biologicals reference database locked, GSK Biologicals will be responsible for initiating the execution of the statistical analysis plan in collaboration with HAS and MVI and breaking the blind.

GSK Biologicals' policy (incorporating ICH E2A guidance, EU Clinical Trial Directive and Federal Regulations) is to unblind any serious adverse event (SAE) report associated with the use of the investigational product, which is unexpected and attributable/suspected, prior to regulatory reporting. The Clinical Safety Physician is responsible for unblinding the treatment assignment in accordance with specified time frames for expedited reporting of SAEs (Refer to Section 8.8).

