### **8.3. Clinical laboratory parameters and other abnormal assessments qualifying as adverse events and serious adverse events**

Abnormal laboratory findings (e.g., clinical chemistry, hematology, urinalysis) or other abnormal assessments (e.g. blood film ) that are judged by the investigator to be clinically significant will be recorded as AEs or SAEs if they meet the definition of an AE, as defined in Section 8.1 or SAE, as defined in Section 8.2. Clinically significant abnormal laboratory findings or other abnormal assessments that are detected during the study or are present at baseline and significantly worsen following the start of the study will be reported as AEs or SAEs.

The investigator will exercise his medical and scientific judgment in deciding whether an abnormal laboratory finding or other abnormal assessment is clinically significant.

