**Table 10 Acceptable/normal ranges for blood testing**

|                            | Acceptable limit/
normal range                                    | Toxicity grading scale                 |                                        |                                        |                                                                   |
|----------------------------|----------------------------------------------------------------------|----------------------------------------|----------------------------------------|----------------------------------------|-------------------------------------------------------------------|
|                            |                                                                      | Grade 1                                | Grade 2                                | Grade 3                                | Grade 4                                                           |
| Hemoglobin                 | $\geq 8.0$ g/dL                                                      | < ULN                                  | < 6.0 g/dL                             | < 5.0 g/dL                             | < 5.0 g/dL &
clinical signs of
heart failure                |
| Total white
cell count† | $\geq 4.0 \times 10^3/\mu\text{L}$
$< 17 \times 10^3/\mu\text{L}$ | $2.5$ to $4.0 \times 10^3/\mu\text{L}$ | $1.5$ to $2.4 \times 10^3/\mu\text{L}$ | $1.0$ to $1.4 \times 10^3/\mu\text{L}$ | $< 1.0 \times 10^3/\mu\text{L}$                                   |
| Platelets†                 | $\geq 100 \times 10^3/\mu\text{L}$                                   | $50$ to $99 \times 10^3/\mu\text{L}$   | $25$ to $49 \times 10^3/\mu\text{L}$   | $< 25 \times 10^3/\mu\text{L}$         | $< 25 \times 10^3/\mu\text{L}$
& clinical signs
of bleeding |
| ALT*                       | $\leq 60$ $\mu\text{mol/L}$                                          | $1.1$ to $2.5 \times \text{ULN}$       | $2.6$ to $5.0 \times \text{ULN}$       | $5.1$ to $10.0 \times \text{ULN}$      | $> 10.0 \times \text{ULN}$                                        |
| Creatinine*                | $\leq 60$ $\mu\text{mol/L}$                                          | $1.1$ to $1.5 \times \text{ULN}$       | $1.6$ to $3.0 \times \text{ULN}$       | $3.1$ to $6.0 \times \text{ULN}$       | $> 6.0 \text{ ULN}$ or
requires
dialysis                    |

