#### **10.8.1.2. Secondary safety endpoints**

Safety will be analyzed on the Total Cohort.

The percentage of subjects with at least one local adverse event (solicited and unsolicited), with at least one general adverse event (solicited and unsolicited) and with any adverse event during the solicited follow-up period will be tabulated with exact 95% CI after each vaccine dose and overall. The percentage of doses followed by at least one local adverse event (solicited and unsolicited), by at least one general adverse event (solicited and unsolicited) and by any adverse event will be tabulated, overall vaccination course, with exact 95% CI. Similar tables will be generated for Grade 3 events, the relationship of the event to vaccination.

The percentage of subjects reporting each individual solicited local and general adverse event during the solicited follow-up period will be tabulated with exact 95% CI. The percentage of doses followed by each individual solicited local and general adverse event will be tabulated, overall vaccination course, with exact 95% CI. Similar tables will be generated for Grade 3 events, the relationship of the event to vaccination and for fever, temperature (in 0.5°C increments).

The proportion of subjects reporting an AE (unsolicited) 30 days post each vaccination, classified by the MedDRA preferred term level, reported from study start until the end of the double-blind phase (visit 6) will be tabulated with exact 95% CI.

Biochemistry (ALT, bilirubin, creatinine) and hematology (hemoglobin, WBC, platelets) values that are outside of the reference ranges will be described for Clinic Visit 6 (end of double-blind phase). Frequency distribution of results by toxicity grades will be tabulated by group.

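### The laboratory safety summary splits values at what is naturally read as the enrolment limit and never uses the screening value; a baseline-adjusted contrast should be added

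*Protocol*

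**What the plan says.** Four parts of the protocol bear on this.

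- **Entry.** Section 4.7 lists as an exclusion "Laboratory screening tests out of range, specifically", and refers to Table 10.
- **The ranges.** Table 10 (section 8.5.1) is titled "Acceptable/normal ranges for blood testing". A single column serves as both acceptable limit and normal range; for hemoglobin it is at least 8.0 g/dL.
- **During the study.** Section 5.6 points to the same table: "For all values outside the normal range (refer to Table 10), the reason and/or clinical condition will be documented".
- **Analysis.** Section 10.8.1.2 says that "values that are outside of the reference ranges will be described for Clinic Visit 6", followed by "Frequency distribution of results by toxicity grades will be tabulated by group". Section 10.9.1 describes out-of-range values again at the end of the single-blind phase. Neither section mentions the screening value, a change from it, or a test on these data.

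The screening value does enter adverse event reporting. Under section 8.3, clinically significant abnormalities that "are present at baseline and significantly worsen following the start of the study will be reported as AEs or SAEs".

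**The concern.** If the limit that admits a child is also the limit that later marks the child as out of range, the screening rate is 0% by construction among eligible children. Any later rate can then look like a post-vaccination rise, although part of it is ordinary within-child variation around a truncated starting point.

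The screening value matters more than usual in this design. Both groups receive RTS,S with MPL and QS21, and there is no group without RTS,S. The between-group table cannot show an effect common to both vaccines, so the child's own screening value is the only internal reference. For the contrast the trial can make, AS01E against AS02D, a split at one limit discards most of the information in a continuous measurement that has a baseline value for each child.

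**Working it through.** The protocol states no expected out-of-range rate, so there is no figure of its own to reproduce. The check uses hemoglobin, the only parameter for which the protocol gives population figures.

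**1. A distribution from the site figures.** Section 4.3 reports that "around 70% of children tested at HAS MRU have Hb < 9g/dL; about 17% of children have Hb < 5g/dL". A normal curve through these two points has

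- SD s = (9 − 5) / (0.524 + 0.954) = 2.71 g/dL
- mean = 9 − 0.524 × 2.71 = 7.58 g/dL

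Under this curve 56% of children fall below 8.0 g/dL and would fail screening on hemoglobin alone. It describes children tested at the research unit. The trial enrols healthy children, so it is best treated as an extreme case.

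**2. Crossing rate with no true change.** Split s² into a between-child part and a within-child part w². Then compute P(second value < 8.0 given first value ≥ 8.0) by numerical integration. The within-child SD w is not in the documents and is assumed, as are all distributions below the first row.

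| Mean / SD (g/dL) | w = 0.2 | w = 0.5 | w = 0.7 | w = 1.0 |
|---|---|---|---|---|
| 7.58 / 2.71 (site fit) | 3.8% | 9.4% | 13.2% | 19.0% |
| 9.5 / 1.2 | 1.9% | 4.8% | 6.6% | 9.1% |
| 10 / 1.5 | 1.4% | 3.4% | 4.7% | 6.5% |
| 10 / 1.2 | 1.0% | 2.4% | 3.2% | 4.3% |
| 10.5 / 1.3 | 0.6% | 1.4% | 1.8% | 2.4% |
| 11 / 1.2 | 0.2% | 0.4% | 0.5% | 0.6% |

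The span is 0.2% to 19.0%. With 90 children per group that is 0.002 × 90 = 0.2 to 0.19 × 90 = 17 children.

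**3. What the toxicity table adds.** Hemoglobin Grade 2 starts below 6.0 g/dL. The same calculation with 6.0 as the lower cut gives 0.02% (w = 0.5) to 1.7% (w = 1.0) under the site fit. Grades 2 and above therefore already separate large falls from small crossings. Almost all chance crossings land between 6.0 and 8.0 g/dL. There Grade 1 is written as below the upper limit of normal, with no upper limit given for hemoglobin.

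**4. Mean change from screening.** Among children admitted at 8.0 g/dL or above, the expected change with no effect is −(w²/s²) × (mean of those admitted − population mean). Under the site fit, those admitted average 2.43 g/dL above the population mean:

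- w = 0.5: −(0.25/7.32) × 2.43 = −0.08 g/dL
- w = 1.0: −(1.00/7.32) × 2.43 = −0.33 g/dL

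Mean change therefore carries its own regression effect. The ANCOVA group contrast does not, because screening precedes vaccination and the groups are randomized.

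**5. Precision of the adjusted contrast.** The correlation of two values is ρ = 1 − w²/s², the residual SD is s√(1 − ρ²), and the 95% half-width with 75 per group is about 1.96 × residual SD × √(2/75). Site fit:

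- w = 0.5: ρ = 0.966, residual SD 0.70, half-width 0.22 g/dL
- w = 1.0: ρ = 0.863, residual SD 1.37, half-width 0.44 g/dL

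For the 10/1.2 population the half-widths are 0.22 and 0.37 g/dL. A useful interval for the group difference is thus available whatever the crossing rate turns out to be.

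**The case against.** **This belongs in the analysis plan.** Section 6.5 says "A formal reporting and analysis plan (RAP) will be developed", and shift tables are commonly specified there. This stands to the extent that the absence of a shift table from the protocol is not itself a finding. What remains is that the protocol does fix a summary, and the one it fixes splits at the entry limit.

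**The shared limit is inferred.** Section 10.8.1.2 does not cite Table 10. It includes bilirubin, which has no row there, and Appendix B has the investigator acquire local normal ranges. Sections 5.6 and 4.7 make Table 10 the natural reading, but they do not settle it.

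**Other provisions give context.** A reason is documented for each out-of-range value (5.6), worsening from baseline is considered for adverse event reporting (8.3), and the grade table isolates large falls. All of this stands. None of it gives a group contrast that uses the screening value.

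**Stronger readings that the documents do not support:**

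- A reader might infer that 9–19% of children will appear newly anemic from measurement noise. That needs both the site fit and a within-child SD of 0.5 to 1.0 g/dL. Such an SD covers biological as well as measurement variation, and newly anemic is not a protocol category.
- A reader might infer a biased comparison between vaccines. Randomization makes the same background expected in both groups.
- A reader might fault the plan for the low power of a Fisher test on out-of-range counts. No such test is planned on these values.
- A reader might want a minimum-fall rule before a value counts as abnormal. That trades away sensitivity in the first study of AS01E in children, and nothing in the documents supports a particular threshold.

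**Conclusion.** The point holds as a modest, nearly free improvement to the analysis. On the natural reading of Table 10, the out-of-range summary starts at 0% among eligible children by construction and ignores the only internal reference the trial has. Some later crossings will reflect within-child variation and regression to the mean. Their rate is unknown: below 1% to about 19% for hemoglobin, depending on an assumed distribution and an assumed within-child SD, with the top of the range tied to a site sample unlike the children to be enrolled. No calculation was made for the other parameters.

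The effect is dilution of a descriptive comparison. It does not touch the coprimary endpoints.

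**What to change.** In section 10.8.1.2, and for Month 14 in section 10.9.1:

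1. Keep the out-of-range counts and the toxicity-grade table, and name the source of the reference ranges, including bilirubin.
2. For each parameter, add the Visit 6 and Month 14 value adjusted for the screening value by ANCOVA (log scale for ALT, bilirubin and creatinine), with the AS01E minus AS02D difference and its 95% CI.
3. Add a descriptive table of screening value by later category, by group.
4. State that mean change from screening is itself subject to regression to the mean, so a within-group fall is not evidence of a vaccine effect.

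The hemoglobin Grade 1 entry and the acceptable limit in Table 10 need to be reconciled so that values from 6.0 to below 8.0 g/dL can be tabulated. Section 10.9.1 calls the last visit Clinic Visit 9, whereas the schedule calls it Clinic Visit 7; this should be aligned.

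Cost: analysis wording and a few extra descriptive tables. Screening laboratory values are already recorded on the CRF, so no samples, visits or children are added.

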### **10.8.2. Analyses of immunogenicity**

The primary analysis will be based on the ATP cohort for analysis of immunogenicity. If the percent of enrolled subjects excluded from this ATP cohort is more than 5%, a second analysis based on the Total Vaccinated cohort will be performed to complement the ATP analysis.

For the secondary immunogenicity endpoint, for anti-HBs GMTs 1 month post Dose 3, the assessment of non-inferiority of the RTS,S/AS01E group versus the RTS,S/AS02D group will be performed by comparing the upper limit of the 95% CI on the ratio of GMTs (RTS,S/AS02D / RTS,S/AS01E group) with a pre-defined non-inferiority limit, set at 3. The analysis will be performed on the ATP cohort for immunogenicity. If more than 5% of subjects are excluded from the ATP cohort for immunogenicity, a second analysis will be performed on the total vaccinated cohort.

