- Blood for safety monitoring of hematology, renal and hepatic function will be measured at screening, one week post Dose 1, one month post Dose 3 and 12 months post Dose 3.

- Anti-CS antibody titers will be determined at screening, one month post Dose 2, one month post Dose 3 and 12 months post Dose 3.
- Anti-HBs antibody titers will be determined at screening, one month post Dose 2, one month post Dose 3 and 12 months post Dose 3.
- CMI and B-cell memory immune responses will be determined at screening, one month post Dose 2, one month post Dose 3 and 12 months post Dose 3.
- Timing of final analysis: 1 month post Dose 3. An annex safety analysis will be performed at the end of the study, one year post Dose 3.
- Data collection: conventional Case Report Form (CRF).

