**Clinic Visit 1: Screening**  
Week -4 to Day 0

---

- Obtain signed, dated, thumb printed informed consent from the parent(s)/guardians
- Check inclusion/exclusion criteria
- Record HBV immunization status
- Take medical history and carry out physical examination
- Record any SAEs that may have occurred as a result of study procedures
- Venous blood sample to collect 5 mL blood for analysis of:
  - hematology (complete blood count)
  - biochemistry (creatinine, ALT and bilirubin)
  - serology (antibodies to CS, HBs)
  - cell-mediated immunity and B-cell memory

---

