**10.5. Estimated sample size**

A sample size of 75 evaluable subjects per group will have 90% power to demonstrate non-inferiority of RTS,S/AS02D versus RTS,S/AS01E in terms of anti-CS immune response (upper limit of 95% CI of the GMC ratio RTS,S/AS02D versus RTS,S/AS01E below 3.0) assuming a log Standard Deviation of 0.9 in both groups, alpha=0.025 (Pass 2000). It will be considered that non-inferiority is reached when the upper limit of the 95% CI of the anti-CS GMC ratio of RTS,S/AS02D to RTS,S/AS01E is below 3.0.

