#### **10.8.2.2. Anti-HBs antibodies**

The percentage of subjects with sero-protective levels of anti-HBs (proportion of subjects with anti-HBs antibody titers greater than or equal to 10 mIU/mL ) with 95% CI will be determined at each blood sampling time point. Antibody titers will be summarized by GMT with 95% CI at all time points at which serological samples are taken. Antibody titers after Dose 3 will also be investigated using reverse cumulative curves.

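### The anti-HBs non-inferiority test is written as an unadjusted GMT ratio, although the screening titer and hepatitis B vaccination status are collected and could sharpen it

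*Protocol*

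**What the plan says.** Section 2.2 of the protocol makes non-inferiority of the anti-HBs response a secondary objective to be demonstrated. Section 10.8.2 gives the rule: "for anti-HBs GMTs 1 month post Dose 3, the assessment of non-inferiority of the RTS,S/AS01E group versus the RTS,S/AS02D group will be performed". The method named there is "comparing the upper limit of the 95% CI on the ratio of GMTs", taken as RTS,S/AS02D over RTS,S/AS01E, and that limit is judged against a margin of 3. No covariate or stratum is named. Section 10.7 defines a GMT as the back-transformed mean of log10 titers, so the ratio as written is unadjusted.

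The baseline information is collected. The screening visit in Section 5.11 includes "Record HBV immunization status". The synopsis states: "Anti-HBs antibody titers will be determined at screening, one month post Dose 2, one month post Dose 3 and 12 months post Dose 3". Table 6 plans the screening titer for all 180 children.

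Section 4.7 excludes non-protocol vaccines only within 30 days of Dose 1, so earlier hepatitis B vaccination is allowed. Section 6.4.2 allocates treatment numbers in order of presentation, without stratification.

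Immunization status is used only for an exploratory anti-CS description (synopsis, Sections 10.4 and 10.9.2.3). For hepatitis B, Section 10.8.2.2 tabulates "The percentage of subjects with sero-protective levels of anti-HBs" at each sampling time, screening included, but does not split later rates by screening status.

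**The concern.** The sample may mix children already primed against hepatitis B with children who are not. If primed children reach higher titers after Dose 3, the mix adds variance to log titer. An unadjusted ratio carries that variance into its confidence interval, while a model with the baseline value removes part of it. The protocol treats immunization status as worth analyzing for anti-CS, yet leaves it out for anti-HBs, the response it bears on most directly.

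At stake is the precision of one secondary non-inferiority conclusion. A smaller point concerns seroprotection. The pooled rate after Dose 3 includes children already at or above 10 mIU/mL before Dose 1. The separate rates at screening and after Dose 3 do not give the rate among children who started below that level.

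**Working it through.** **Inputs from the protocol.** Margin 3, so log10(3) = 0.477. Section 10.5 states: "A sample size of 75 evaluable subjects per group will have 90% power to demonstrate non-inferiority", "assuming a log Standard Deviation of 0.9 in both groups, alpha=0.025 (Pass 2000". That calculation is for anti-CS; none is given for anti-HBs.

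**Reproducing the stated figure.** n per group = 2 × [0.9 × (1.960 + 1.282) / 0.477]² = 74.8, rounded up to 75. At 75 per group the standard error is 0.9 × √(2/75) = 0.147, and power = Φ(0.477/0.147 − 1.960) = 90.1% (89.7% by noncentral t). The 0.9 must be on the log10 scale, since a natural-log reading gives 15 per group. The anti-CS figure is correct.

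**Gain from adjustment (assumed inputs).** ANCOVA on a baseline with correlation ρ gives residual SD = SD × √(1 − ρ²). With 75 per group, a true ratio of 1 and a total log10 SD of 0.9 borrowed from anti-CS:

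| ρ | residual SD | power | 95% CI factor | n per group for 90% power |
|---|---|---|---|---|
| 0 | 0.900 | 90.1% | 1.95 | 75 |
| 0.3 | 0.859 | 92.6% | 1.89 | 69 |
| 0.5 | 0.779 | 96.3% | 1.78 | 57 |
| 0.7 | 0.643 | 99.5% | 1.61 | 39 |

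With a total SD of 0.6, power is at least 99.8% throughout, so adjustment hardly matters. With a total SD of 1.2, power runs 68.3%, 72.3%, 80.3% and 92.6% over the same correlations.

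**Chance imbalance is part of the same variance.** Assume half the children are primed, primed titers are 1 log10 higher, and the within-stratum SD is 0.8.
- Total SD = √(0.8² + 0.25 × 1²) = 0.943.
- 95% half-width, unadjusted: 1.96 × 0.943 × √(2/75) = 0.302 log10.
- 95% half-width, adjusted: 1.96 × 0.8 × √(2/75) = 0.256 log10.
- √(0.302² − 0.256²) = 0.160 log10.
- 95% range of chance imbalance in primed share: 1.96 × √(2 × 0.25/75) = 0.160, or 16 points. At a 1 log10 gap this shifts the ratio by 10^0.160 = 1.45-fold.

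The two values of 0.160 are the same quantity. The unadjusted interval already covers the imbalance, and its factor widens only from 10^0.256 = 1.80 to 10^0.302 = 2.00.

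**Seroprotection (assumed inputs).** Let b be the share protected at screening, assumed to stay protected, and r the rate reached among the rest. The pooled rate is b + (1 − b)r, which exceeds r by b(1 − r).
- b = 0.2, r = 0.97: 0.2 × 0.03 = 0.6 points.
- b = 0.8, r = 0.97: 0.8 × 0.03 = 2.4 points.
- b = 0.8, r = 0.80: 0.8 × 0.20 = 16 points.

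Over b from 20% to 80% and r from 80% to 97%, the excess is 0.6 to 16 points.

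**The case against.** The strongest reply is that covariates and subgroup tables belong in the reporting and analysis plan announced in Section 6.5, which is not shown. Section 10.8.2 does not use the word unadjusted. This stands in part, since the plan may add such analyses. But the protocol itself fixes both the estimator, through Section 10.7, and the decision rule, so an adjusted ratio as the main test would depart from its text.

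Three further replies stand and limit the point:
- An unadjusted ratio from a 1:1 randomized trial is unbiased, and no stated figure is wrong.
- The screening titer is not wholly ignored. Section 10.8.2.2 shows by group how many children were protected before Dose 1, and the objective in Section 2.2 is only to describe seroprotection.
- Every anti-HBs size is assumed. Section 1.4 describes a high response to RTS,S/AS02A whatever the prior HBs serostatus. That does not say titers were equal, but it leaves the size of any gap open.

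A reader might infer that the test is underpowered. Taking 0.9 as the within-stratum SD, with half the children primed and a 1 log10 gap, gives a total SD of √(0.81 + 0.25) = 1.03 and power of 81% against 90% adjusted. The protocol does not support this, because its 0.9 is an anti-CS value and nothing identifies it as a residual SD for anti-HBs. A reader might also count the 1.45-fold imbalance shift as a bias or an added harm, but it is already inside the interval.

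**Conclusion.** The point holds as one of efficiency. The secondary anti-HBs test leaves out baseline information that is already collected, and adjustment would narrow the interval if that information is prognostic. At 75 per group and an assumed total log10 SD of 0.9, the gain is about 2.5 to 9.5 power points for correlations of 0.3 to 0.7. It is larger if the SD is larger, and about nil if the SD is near 0.6 or the correlation near 0. The protocol does not allow a choice among these cases.

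It might be inferred that the seroprotection result is seriously inflated. The documents do not show that. If about 97% of initially unprotected children become protected, the pooled excess is 0.6 to 2.4 points. The 97% is borrowed from the overall RTS,S/AS02A rate at 18 months after Dose 3 in Section 1.4, not from initially unprotected children. The rate in that group is still worth reporting, because the planned tables do not give it.

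Nothing here supports changing the coprimary anti-CS analysis, which is a different response with no such case made for it. The change is worth making before unblinding, but the main conclusion of the trial does not depend on it.

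**What to change.** - **Section 10.8.2:** estimate the anti-HBs GMT ratio by ANCOVA on log10 titer one month after Dose 3, with group, screening log10 anti-HBs and, where documented, hepatitis B immunization status. Compare the upper 95% limit of the adjusted RTS,S/AS02D to RTS,S/AS01E ratio with 3. Keep the unadjusted ratio as a sensitivity analysis.
- **Section 10.8.2.2:** add, by group, descriptive post-vaccination seroprotection with 95% CI among children below 10 mIU/mL at screening.

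The cost is one model, one table and a few lines of text, with no new data collected. Immunization status may be undocumented for some children, so the text should say how they are handled, for example with a category of their own so that they stay in the model. Stating this before unblinding matters, because adjustment chosen after an imbalance has been seen is open to dispute.
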